## **8. CLINICAL TRIAL TERMINATION CRITERIA**

The Sponsor reserves the right to terminate the clinical trial for safety or administrative reasons at any time. If the Sponsor, Principal Investigator, Data Safety Monitoring Board (DSMB), Institutional Review Board (IRB), or Food and Drug Administration (FDA) officials discover conditions during the study indicating that the trial or participation by a clinical site should be discontinued, this action may be taken after appropriate consultation between the Sponsor and the Investigators.

Conditions that may warrant discontinuation of the trial at a specific clinical site may include the following:

- Failure of the Investigator to enroll patients into the trial at an acceptable rate (as defined and agreed upon between the Investigator and the Sponsor).
- Failure of the Investigator to comply with the pertinent FDA regulations.
- Submission of false information by the Investigator from the research facility to the Sponsor or the FDA.

Conditions that may warrant discontinuation of the trial may include, but are not limited to, the following:

- Discovery of an unexpected, serious or unacceptable risk to the patients enrolled in the study.
- Decision on the part of the Sponsor to suspend or discontinue testing, evaluation or development of the study product at any time.

## **9. SAFETY**

### **9.1. ADVERSE EVENTS**

An Adverse Event is any sign, symptom, illness, clinically significant abnormal laboratory value or other adverse medical event that appears for the first time or worsens in a subject (control or treatment arm) during this clinical study, regardless of whether or not it is considered related to the device.

## **9.2. SERIOUS ADVERSE EVENTS**

Any Adverse Event, whether considered study-treatment related or not, which fits any of the criteria below, is considered a serious adverse event (SAE):

- Results in death
- Is life-threatening (meaning that the patient was at risk of death at the time of the event; this does not refer to an event which might have caused death if it had occurred in a more severe form)
- Requires in-patient hospitalization or prolongs the existing hospitalization
- Is a persistent disability/incapacity
- Is a congenital anomaly or birth defect
- Is considered an important medical event by the Principal Investigator (e.g., surgery, return to ICU, emergency procedures)

## **9.3. UNANTICIPATED ADVERSE DEVICE EFFECT**

Unanticipated adverse device effect (UADE) is any serious adverse effect on health or safety, any life-threatening problem or death caused by, or associated with a device, if that effect, problem, or death was not previously identified in nature, severity, or degree of incidence in the application; or any other unanticipated serious problem associated with a device that relates to the rights, safety, or welfare of subjects.

## **9.4. ANTICIPATED ADVERSE EVENT**

Co-morbidities and symptoms/laboratory/physiological deviations normally associated with pre-existing conditions (e.g., diabetes, ASHD, other C-V conditions, pneumonia, dialysis shunt problems, neurologic deficits) are considered “anticipated adverse reactions.” The investigator is required to take special care in differentiating concomitant illness events from those related to the randomized therapy by use of patient history, relationship to treatment time and cartridge integrity, and other characteristics of clinical circumstances present at the time of the adverse experience, including drug interactions of concomitant medications and effects of surgical and/or medical procedures.

Adverse events associated with CRRT or underlying critical illness are also to be considered “anticipated”. Such events include, but are not limited to: thrombocytopenia, hyponatremia, hypokalemia, hypo- or hypercalcemia, hypo- or hyperglycemia, air embolism, hypotension, hemolysis, increased oxygenation requirements, leukopenia, arrhythmias, hypothermia, lactic acidosis, temporary decrease in cardiac output or cardiac index, disruption of skin integrity, bleeding, shock, bacteremia, hypotension, and death.

There are many anticipated events in the ICU patient that are not listed here. Any questions as to the expectedness of an adverse event will be discussed with CytoPherx’s CMO and/or the DSMB.

## **9.5. CAUSALITY**

All randomized patients must have all AEs assessed for causality (probability that the AE may have been caused by the study treatment) by the Principal Investigator. The following definitions for causality assessment will be used in this study:

### **9.5.1. DEFINITELY RELATED**

A clinical event, including a significant change in a laboratory test, that occurs in a plausible time relationship to the SCD treatment or other protocol-required activity, and which cannot be explained by concurrent disease or other drugs, chemicals, or procedures and that follows a clinically reasonable response upon withdrawal of the SCD treatment.

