### **2.4.2. SAFETY**

A summary of all adverse events (AEs) observed in the 35 subjects are summarized in Table 7. A total of 199 adverse events were observed in 33 of the 35 subjects. Of these 199 AEs, 12 were deemed to be possibly related and 1 deemed definitely related (as determined by the investigator) to the study therapy. These included worsening coagulation defect, hypotension, neutropenia, DIC, thrombocytopenia, recurrent renal failure, hypophosphatemia, hypercalcemia, anemia, and cardiogenic shock. (Thrombocytopenia is frequently encountered during administration of CRRT therapy alone [22] and neutropenia is a known consequence of critical illness and/or sepsis [23]).

One of these 13 related events, one event was deemed to be “definitely” related to therapy which was coded as “Metabolic Alkalosis Secondary to Citrate.” Although this was the name given to the event by the PI, the event in question was a case of severe hypocalcemia which resulted from the initiation of citrate anticoagulation and which resulted in termination of therapy 2 hours after initiation. Citrate intolerance is a known side effect of citrate anticoagulation in the setting of liver disease. In some patients, citrate quickly builds up and leads

to metabolic alkalosis and hypocalcemia [24]. In this subject, the citrate intolerance was quickly recognized and therapy was discontinued 2 hours after initiation.

Two subjects experienced thrombocytopenia which was deemed possibly related to the therapy and one required platelet transfusions. There were 8 additional incidences of thrombocytopenia in 8 subjects that were deemed as unrelated by the PI. Four of these 8 subjects required platelet transfusions. As stated above, thrombocytopenia is frequently encountered during administration of CRRT therapy alone [22] and is often a consequence of the types of critical illnesses (e.g., bone marrow suppression, SIRS, sepsis, drug reactions) observed in the ICU setting. For example, in a retrospective analysis of a 71 patient cohort in the ICU on systemic heparin anticoagulation who received CRRT, 31 patients (44%) experienced severe thrombocytopenia [22].

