### **9.5.3. POSSIBLY RELATED**

A clinical event, including a significant change in a laboratory test, that occurs within a reasonable time sequence in relationship to the SCD treatment or other protocol-related activity that could also be explained by concurrent disease, drugs, chemicals, or procedures. The clinical course after withdrawal of the SCD treatment may be unclear with respect to the contribution of the SCD treatment to the AE.

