## 11. DATA SAFETY MONITORING BOARD

An independent Data Safety Monitoring Board (DSMB) will review safety results over the course of the study on a schedule set by CytoPherx, Inc. and the DSMB. In addition, the DSMB will be provided with one formal interim statistical analysis on the primary endpoint of 60 day mortality, as detailed in the statistical analysis section below. The DSMB will comply with the FDA Guidance: “Guidance for Clinical Trial Sponsors on the Establishment and Operation of Clinical Trial Data Monitoring Committees”. The DSMB will be formed to provide scientific and medical feedback for the study.

The DSMB will focus on the following areas:

- *Performance* – to assess study conduct and compliance;
- *Effectiveness* – to assess mortality;
- *Safety* – to assess the incidence, severity, relationship, and timing of adverse events and to identify safety concerns; and
- *Context* – to assess the study relative to the AKI literature.

The DSMB will consist of a minimum of 5 independent experts including a minimum of 4 clinicians and a biostatistician. The DSMB will operate under a charter and will identify prospective data display specifications to conduct independent data reviews. The DSMB will make recommendations to the Sponsor to continue the study as planned or to stop the study due to safety or futility issues. The DSMB will meet to perform safety and effectiveness evaluations and to provide feedback to the Sponsor at least annually as well as after 25% and 50% of the cohort has completed 60 day follow-up. The DSMB reserves the right to request more frequent evaluations.

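### Section 9.5 requires causality grading in both arms, but its two upper related grades can be reached only by patients who received the SCD

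*Protocol*

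**What the plan says.** Section 9.5 sets the scope: "All randomized patients must have all AEs assessed for causality". It describes causality as the "probability that the AE may have been caused by the study treatment". Section 9.4 likewise asks the investigator to take care in "differentiating concomitant illness events from those related to the randomized therapy".

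Sections 9.5.1 to 9.5.4 then define four grades. For *definitely related*, the timing condition is that the event "occurs in a plausible time relationship to the SCD treatment or other protocol-required activity". A further condition, joined by *and*, is "and that follows a clinically reasonable response upon withdrawal of the SCD treatment". Section 9.5.2 (*probably related*) ends with the same withdrawal clause. Section 9.5.3 (*possibly related*) does not require a response to withdrawal. It covers an event occurring within a reasonable time "in relationship to the SCD treatment or other protocol-related activity that could also be explained by concurrent disease, drugs, chemicals, or procedures". *Unrelated* (9.5.4) requires that an association with the SCD or study activity be improbable.

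Three other places bear on this. Sections 6.2.1 and 6.2.2 make citrate anticoagulation mandatory in both arms. Section 7.2.1 lists CRRT-related medical events (item 2, judged by relationship to the control arm) separately from SCD-related medical events (item 3). Section 11 charges the DSMB, among other things, "to assess the incidence, severity, relationship, and timing of adverse events".

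**The concern.** The scale is to be applied in both arms, and its timing condition is worded to reach activity that both arms share. The withdrawal condition names the SCD alone and offers no alternative for stopping CRRT, citrate or any other protocol activity. An arm that never receives the SCD cannot show a response to its withdrawal.

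At stake is the meaning of the relatedness ratings. If the DSMB, or a later safety table, sets related events side by side by arm, the two upper grades will hold SCD-arm events only, whatever happens in the controls. The trial is open-label (section 4), so investigators apply the scale knowing the assignment. The ratings are made at the site under definitions fixed in the protocol. A later analysis could not correct them without grading the events again.

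**Working it through.** The protocol gives no figure to reproduce. The check is whether an event in a control patient can satisfy each definition.

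| Grade | Timing condition | Other explanation | Response to withdrawal | Open to a control event? |
|---|---|---|---|---|
| Definitely (9.5.1) | SCD or other protocol activity | Must be ruled out | Required, SCD only | No |
| Probably (9.5.2) | SCD or other protocol activity | Must be unlikely | Required, SCD only | No |
| Possibly (9.5.3) | SCD or other protocol activity | Must be available | Not required | Yes, if another explanation exists |
| Unrelated (9.5.4) | Association improbable | Must be likely | Not required | Yes |

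In the first two rows a control event passes the timing condition, because required citrate is a protocol activity, and fails only on the last. Two of the three related grades are therefore closed to controls.

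**Against section 7.2.1.** Item 2 asks the investigator to judge whether an event such as persistent thrombocytopenia is related to the control arm, and item 3 asks the same for the SCD. The protocol therefore expects relatedness to control therapy to be judged, but the section 9.5 scale cannot express it above *possibly*.

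**Illustration from pilot ARF-002** (section 2.4.2 and Table 7):

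- Related events: 12 possibly + 0 probably + 1 definitely = 13.
- Share of all events: 13 / 199 = 6.5%.
- Upper grades among related events: 1 / 13 = 7.7%.
- *Possibly* among related events: 12 / 13 = 92.3%.

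Of the single upper-grade event the protocol says that "the event in question was a case of severe hypocalcemia which resulted from the initiation of citrate anticoagulation". Citrate is required in both arms of the present trial. The same event in a control patient here could not be graded definitely related.

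**Where relatedness is used.** Section 11 includes it in the DSMB's review. Section 12.7 summarizes adverse events by arm, repeats this for serious events and those leading to discontinuation, and tests incidence with Fisher's exact test. It states no table or test by relatedness.

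**The case against.** The best counter-argument is that the scale is meant to rate the investigational device. Unanticipated adverse device effects (9.3) are defined by the device, and it is correct that patients without a device have no events caused by it. The term *study treatment* can be read that way: section 6.2.2 calls the SCD arm the study treatment arm, section 6.4 contrasts control with study therapy, and section 7.2.2 glosses study therapy as CRRT plus SCD. This reading is possible, but section 9.5 does not state it. The wider timing condition, the reference to randomized therapy in 9.4 and item 2 of 7.2.1 all point the other way. If it is what was meant, the protocol needs to say so.

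The withdrawal clause also limits the SCD arm. An SCD patient whose device was not withdrawn, or whose response to withdrawal was uninformative, cannot reach the upper grades either. That is true, but the SCD arm can meet the condition and the control arm cannot.

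Three stronger conclusions might be inferred, and the document does not support them.

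- *A control reaction to citrate with no competing cause fits no grade.* On a strict reading it does not. But citrate can be read as a drug or chemical and CRRT as a procedure, and then 9.5.3 accommodates the event. On that same reading an SCD-arm citrate event would also fail *definitely*, because 9.5.1 excludes events explained by other drugs, chemicals or procedures. The definitions leave this open.
- *The DSMB could not tell a device signal from background-circuit events.* Both arms receive the sponsor's CRRT equipment and citrate, so all-cause incidence by arm makes that separation without any causality rating. The DSMB also sees severity and timing.
- *The control count of upper-grade events is fixed at 0 of 172.* The zero follows from the wording, but 172 is the number randomized per arm. Adverse events are analyzed in the safety set, which is treated patients by treatment received (12.3, 12.7).

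The pilot is only an illustration. It had no concurrent control arm, and its causality definitions are not shown.

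**Conclusion.** The definitions are wrong as written. Section 9.5 requires grading in both arms, while 9.5.1 and 9.5.2 contain a condition that no patient without the SCD can meet, and this conflicts with section 7.2.1 item 2. Upper-grade related events are SCD-only by construction in the DSMB's review of relationship.

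The effect is confined to relatedness ratings and to any review or table built on them. *Possibly related* remains open to controls, so a pooled count of related events would be skewed but not confined to the SCD arm. If the pilot's distribution were a guide, few events would be in the upper grades. The comparisons of all adverse events, serious events and events leading to discontinuation in 12.7 do not depend on relatedness and are unaffected.

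The conclusion assumes that the word *and* in 9.5.1 and 9.5.2 is applied as written, and that control patients do not receive the SCD. How far the skew would influence the DSMB depends on its charter, which is not shown. This should be corrected, but it does not threaten the trial's main comparisons.

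**What to change.** Either of two changes resolves the conflict.

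1. Reword 9.5.1 to 9.5.4 so that each grade refers to the assigned study therapy or protocol-required activity, and the withdrawal condition refers to withdrawal of that therapy or activity. Reconcile the result with 7.2.1 items 2 and 3.
2. Alternatively, state in 9.5 that the scale rates relatedness to the SCD only and that counts of related events are not to be compared between arms. The timing wording and 7.2.1 item 2 would then need to agree with that statement.

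Rating the circuit, the citrate and the cartridge separately is an optional refinement. It would cost the investigator extra judgments on components that run in series, and the correction does not need it.

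The cost is a few lines of definition text and matching instructions on the adverse event form. Any events already graded under the present wording would need to be graded again for consistency. Sample size, the primary analysis and the comparisons in 12.7 do not change.

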### **9.5.2. PROBABLY RELATED**

A clinical event, including a significant change in a laboratory test, that occurs within a reasonable time sequence in relationship to the SCD treatment or other protocol-required activity that is unlikely to be attributed to concurrent disease, other drugs, chemicals, or procedures, and that follows a clinically reasonable response upon withdrawal of the SCD treatment.

### **9.5.3. POSSIBLY RELATED**

A clinical event, including a significant change in a laboratory test, that occurs within a reasonable time sequence in relationship to the SCD treatment or other protocol-related activity that could also be explained by concurrent disease, drugs, chemicals, or procedures. The clinical course after withdrawal of the SCD treatment may be unclear with respect to the contribution of the SCD treatment to the AE.

### **9.5.4. UNRELATED**

An AE, including a significant change in a laboratory test, that occurs with a temporal relationship to the SCD treatment or protocol-required activity that makes an association with the SCD treatment or study activity improbable, and in which other drugs, procedures or underlying disease(s) provide likely explanation.

## **9.6. SEVERITY – INTENSITY**

The intensity of all adverse events should be evaluated using the following definitions:

### **9.6.1. MILD**

An event that requires minimal clinical treatment or an adverse event requiring monitoring but no intervention or treatment; causes slight discomfort.

**9.6.2. MODERATE**

An event that requires non-routine intervention, (i.e., a new clinical treatment or diagnostic procedure), administered within an hour of the event; causes annoying discomfort.

**9.6.3. SEVERE**

An event requiring immediate intervention; causes significant discomfort.

**9.7. ADVERSE EVENT REPORTING**

Adverse event reporting requirements will be based on the time period in which the adverse event occurs.

**9.7.1. SCREENING PERIOD (CONSENT THROUGH RANDOMIZATION)**

Only adverse events, serious and not serious, directly related to the screening procedures will be captured during this period. Unrelated clinical adverse events that occur prior to randomization will be considered part of the medical history.

**9.7.2. RANDOMIZATION THROUGH END OF STUDY**

All adverse events that occur from the time of randomization/enrollment will be recorded as follows:

- Serious Adverse Events (identified in 9.2) will be recorded until Day 60 after randomization, death, or patient withdrawal of study consent, whichever occurs first.
- Non-serious adverse events will be recorded until Day 60 after randomization, death, patient withdrawal of study consent or until hospital discharge, whichever occurs first.

Any serious adverse event (regardless of relationship to the treatment) occurring from the time of enrollment/randomization through end of study must be reported to CytoPherx Inc, or designee, within 24 hours of knowledge of the event. This includes patients in the control arm.

Each clinical trial site will be supplied with written SAE reporting instructions, SAE reporting forms and contact information for reporting of serious adverse events.

For any AE that is ongoing at the time of the initial report, periodic follow-up information will be required until the adverse event is resolved or the patient is no longer in the study, whichever occurs first.

The Investigator is responsible for all adverse events reporting to the Institutional Review Board (IRB) according to the requirements of the IRB and for providing clinical trial monitors with all medical records needed to source-verify the adverse events.

## 10. CLINICAL EVENTS COMMITTEE

A clinical events committee (CEC) will be in place to review and adjudicate certain events that occur. At the onset of the trial, the CEC will establish a charter that outlines the criteria for which an event requires review, the method in which the reviews will take place, and the minimum documentation required for reviews. The CEC will be made up of physicians based on their clinical expertise and experience on CECs. They will have no other association with this trial or the sponsor. The CRO will have the primary role in composing and managing the CEC.

## 11. DATA SAFETY MONITORING BOARD

An independent Data Safety Monitoring Board (DSMB) will review safety results over the course of the study on a schedule set by CytoPherx, Inc. and the DSMB. In addition, the DSMB will be provided with one formal interim statistical analysis on the primary endpoint of 60 day mortality, as detailed in the statistical analysis section below. The DSMB will comply with the FDA Guidance: “Guidance for Clinical Trial Sponsors on the Establishment and Operation of Clinical Trial Data Monitoring Committees”. The DSMB will be formed to provide scientific and medical feedback for the study.

The DSMB will focus on the following areas:

- *Performance* – to assess study conduct and compliance;
- *Effectiveness* – to assess mortality;
- *Safety* – to assess the incidence, severity, relationship, and timing of adverse events and to identify safety concerns; and
- *Context* – to assess the study relative to the AKI literature.

The DSMB will consist of a minimum of 5 independent experts including a minimum of 4 clinicians and a biostatistician. The DSMB will operate under a charter and will identify prospective data display specifications to conduct independent data reviews. The DSMB will make recommendations to the Sponsor to continue the study as planned or to stop the study due to safety or futility issues. The DSMB will meet to perform safety and effectiveness evaluations and to provide feedback to the Sponsor at least annually as well as after 25% and 50% of the cohort has completed 60 day follow-up. The DSMB reserves the right to request more frequent evaluations.

